## Data management

All the data from this project will be managed by the Paediatric Research Registrar using paper based case record forms (CRF) to record the information at first postnatal (72hr) visit and 6 month postnatal visit. All CRFs will be designed in TELEform™ Elite version 10.5 (https://teleform.software.informer.com/10.5/). Completed CRFs will be checked on the day of completion and any errors, discrepancies or out of range values will be corrected and initialed by the Paediatric Research Registrar. Original copies of the CRF will be held in the PNGIMR WANTAIM Office in a locked filing cabinet accessible only by the Paediatric Research Registrar and the Trial Coordinator. Data entry and review will be ongoing throughout the entire trial period and will be conducted in accordance with WANTAIM study-specific SOPs. Completed CRFs will be electronically scanned at the PNGIMR WANTAIM Office, as completed using a Kodak ScanMate i940 portable scanner, into a computer using a Tagged Image File Format (TIFF). Data will be stored in a dedicated electronic folder prior to verification using TELEform™. A copy of the locally-held data will then be uploaded into a Microsoft SQL spreadsheet before importing into STATA (Stata 14.2, College Station, Texas, United States) for analysis. Electronic versions of the locked datasets and TIFF files for this study will be maintained as part of the PNGIMR’s research studies database. Access to the trial database will be limited to the trial Paediatric Research Registrar, and Principal Investigators. After completion of data analyses, copies of the final database and analytical datasets (neither of which will contain any subject identifying information) will be maintained on secure high-end computers located at the PNGIMR.

## Sample size

The maximum sample size will be determined by the number of women in WANTAIM who deliver during the study period. The required sample size is determined by the required precision around the estimates of sensitivity, the primary outcome. Based on projections of trial enrolment at the study clinics, an estimated 400 women will be invited to participate. If 95% have a 72-hour post-natal visit and 90% of mothers agree to foot length measurement and follow up, there will be 342 neonates. If sensitivity is 70-90%, 95% confidence intervals will be +/- 4 to 5%, which is an acceptable level of precision. If 80% of these infants are followed up at 6 months, we will have repeated anthropometric and physical development measurements on 274 infants. This sample size also ample statistical power for secondary outcomes, such as differences in the mean foot length at birth between infants who have or have not reached one or more developmental milestones. Assessment of the reliability of foot length measurements by community reporters will be measured using the kappa statistic (κ). Based on a published study,18 if agreement is fair between two raters’ measurements of a foot length <8cm, 143 pairs of observations are needed for an estimate of κ=0.4 and its 95% confidence interval. We will therefore enrol 150 consecutive babies for this assessment.

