# Study Objectives

The primary objective of this Neonatal Foot Length (Neofoot) study is to determine the diagnostic accuracy of foot length measurement to predict preterm birth and low birth weight in rural PNG.

Secondary objectives are to:

1. Compare foot length, MUAC and head circumference as predictors of preterm birth and low birth weight
2. Validate a specific foot length cut-off or derive a new cut-off appropriate for PNG
3. Assess the feasibility of using foot length as a measure for preterm birth and low birth weight in the community and health centre by community reporters/volunteers and health centre staff.
4. Determine associations between foot length at birth, physical growth and development of the infant at 6 months, according to study arm.

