## Statistical analysis

I will examine the distributions of each variable. I will describe continuous variables using histograms, mean and standard deviation, and median and interquartile range. I will describe frequencies of categorical variables as percentages. I will conduct a descriptive analysis to examine associations with preterm delivery and low birth weight, including social and demographic factors (collected during WANTAIM assessments) and achievement of developmental milestones at 6 months and between study arms and achievement of developmental milestones at 6 months. I will assess the correlation between the gestational age at birth (measured by USS) and birthweight (measured using digital scales) and anthropometric measures (foot length, head circumference, MUAC) using Spearman’s rank correlation coefficient.

I will calculate diagnostic performance of foot length as: a) sensitivity (proportion of newborns correctly identified as preterm, low birthweight or very low birth weight); and b) specificity (proportion of newborns correctly identified as not preterm or not low birth weight) for 1mm increments in foot length. I will also calculate sensitivity and specificity for head circumference (1.0cm increments) and MUAC (1mm increments).8

To assess the diagnostic performance of each anthropometric measure as a predictor of preterm birth, low birth weight and very low birth weight, I will construct receiver operating characteristic (ROC) curves.24 The ROC curve is a graphical plot of sensitivity (vertical axis) against 1 minus specificity (horizontal axis) for each increment in measurement of the anthropometric measure. The best cut-off for each measure is the value at which the sensitivity and specificity are highest. I will then calculate the area under the curve (AUC, with 95% confidence intervals) as a proportion of the total area. The closer the AUC value is to one, the better the predictive value.

I will provide the best cut-off for the prediction of preterm birth, low birth weight and very low birth weight using foot length, head circumference and MUAC. I will recommend the most appropriate and simple measure based on my findings.

I will use linear regression to examine associations between the foot length at birth and achievement of developmental milestones, with multivariable models to control for potential confounding.

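### The stated ±4 to 5% precision for sensitivity fits only a denominator near all 342 neonates, not the affected newborns among whom sensitivity is estimated

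*Protocol*

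**What the plan says.** The primary objective (Protocol, Study Objectives) is "to determine the diagnostic accuracy of foot length measurement to predict preterm birth and low birth weight in rural PNG". The Sample size section makes sensitivity the quantity that governs size: "The required sample size is determined by the required precision around the estimates of sensitivity, the primary outcome". It starts from the number of women approached ("an estimated 400 women will be invited to participate") and reduces it: "If 95% have a 72-hour post-natal visit and 90% of mothers agree to foot length measurement and follow up, there will be 342 neonates". The precision claim follows at once: "If sensitivity is 70-90%, 95% confidence intervals will be +/- 4 to 5%, which is an acceptable level of precision".

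The section gives no prevalence of preterm birth or low birth weight and no expected number of affected newborns; neither appears elsewhere in the Protocol. The Eligibility criteria describe women already in the parent trial who have ultrasound dating and a postnatal visit within 72 hours. Nothing there selects for small or early babies.

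The Statistical analysis section describes "sensitivity (proportion of newborns correctly identified as preterm, low birthweight or very low birth weight" and plans cut-offs for three targets: "I will provide the best cut-off for the prediction of preterm birth, low birth weight and very low birth weight".

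**The concern.** Sensitivity for preterm birth is the fraction of preterm newborns whose foot length falls below the cut-off. Term newborns contribute to specificity and add nothing to the precision of sensitivity. A precision statement for sensitivity therefore needs the number of cases, and the Sample size section supplies only the number of newborns.

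That sentence is the Protocol's only argument that the study is large enough for its primary outcome, and it calls the precision acceptable. If the denominator is wrong, the study will report much wider intervals than its readers, funders and ethics committees were led to expect. The recommended cut-off and measure will also rest on far fewer infants than the 342 suggests.

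**Working it through.** **Inputs.** From the Sample size section: 400 women invited, 95% with a 72-hour visit, 90% agreeing, sensitivity 70–90%, 95% confidence, stated half-width 4 to 5 percentage points. The prevalence of each target condition is not in the Protocol, so it is treated below as an assumption and shown as a range.

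**Step 1: number of neonates.** 400 × 0.95 × 0.90 = 342, as stated.

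**Step 2: reproduce the stated precision.** The usual (Wald) half-width is 1.96 × √(p(1 − p)/n). With n = 342:

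- p = 0.70: 1.96 × √(0.21/342) = 4.9 points
- p = 0.80: 1.96 × √(0.16/342) = 4.2 points
- p = 0.90: 1.96 × √(0.09/342) = 3.2 points

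The exact 95% intervals with n = 342 are 64.7–74.7% at 70% and 86.4–93.0% at 90%, so the longer, lower arm is about 5 and about 4 points. The stated range is thus recovered by the Wald formula for 70–80%, and by the exact lower arm across 70–90%, when every neonate is in the denominator.

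**Step 3: cases needed for the stated precision.** This step uses no prevalence. The required number of affected newborns is 1.96² × p(1 − p)/h²:

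- ±5 points at 70%: 3.8416 × 0.21/0.0025 = 322.7, so 323 cases, 94% of 342
- ±4 points at 90%: 3.8416 × 0.09/0.0016 = 216.1, so 217 cases, 63% of 342
- most lenient pairing, ±5 points at 90%: 3.8416 × 0.09/0.0025 = 138.3, so 139 cases, about 40% of 342

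Even if half of the newborns were affected (171 cases), the half-width at 70% sensitivity would be 6.9 points.

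**Step 4: half-width on affected newborns.** The formula is that of Step 2, with n = 342 × assumed prevalence:

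| Assumed prevalence | Cases | Half-width at 70% | at 80% | at 90% | Ratio to n = 342 |
|---|---|---|---|---|---|
| 10% | 34 | 15.4 | 13.4 | 10.1 | 3.2 |
| 15% | 51 | 12.6 | 11.0 | 8.2 | 2.6 |
| 20% | 68 | 10.9 | 9.5 | 7.1 | 2.2 |
| 25% | 86 | 9.7 | 8.5 | 6.3 | 2.0 |

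The ratio is 1/√prevalence, apart from rounding of cases. Preterm birth and low birth weight are separate targets, so each has its own row.

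**Step 5: specificity, for comparison.** Its denominator is the unaffected newborns: 342 − 68 = 274 at 20% prevalence and 342 − 34 = 308 at 10%. (This 274 merely coincides with the Protocol's number followed up at 6 months.) The half-width is 5.4 to 5.1 points at 70% specificity and 3.6 to 3.4 at 90%. A figure close to the stated one therefore suits specificity, not sensitivity.

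**The case against.** **The denominator is inferred.** The Protocol prints no formula, and the Wald half-width at 90% with 342 is 3.2 points, outside the stated range. This stands as a caution about how the figure arose. It does not rescue the figure: Step 3 shows that the stated precision is out of reach without an implausible share of affected newborns, however it was computed.

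**The factor of two to three is not a fact from the Protocol.** It corresponds to a prevalence of about 25% down to 11%. Below that range the widening is greater, and above it less. It can be stated only as conditional on the assumption.

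**A reader might infer that sensitivities of 70% and 85% could not be told apart.** That is too general. An observed 70% has a Wald upper limit of 70 + 15.4 = 85.4% with 34 cases, but 82.6% with 51 and 80.9% with 68. The statement fits only the lowest case count shown.

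**A reader might infer that the analysis will use the wrong denominator too.** The definition of sensitivity in the Statistical analysis section is loose, because it does not confine the newborns to affected ones. But the same section builds ROC curves in the standard way ("The ROC curve is a graphical plot of sensitivity (vertical axis) against 1 minus specificity (horizontal axis") and calculates areas under them, which presupposes the correct denominators. This calls for clearer wording and is not a second error.

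**A reader might infer that the very-low-birth-weight cut-off has to be dropped.** Cases will probably be very few, but that target is not in the primary objective and no precision is claimed for it. Whether to report a cut-off is a matter of judgement, provided its uncertainty is shown.

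**Enrolment is capped by deliveries in the parent trial, and intervals calculated from the actual cases will be valid.** Both are true. The harm is therefore a misleading planning statement, not an invalid analysis.

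**Conclusion.** The concern holds. The claim of ±4 to 5 points for sensitivity is wrong as written. It matches a denominator near all 342 neonates, and meeting it on affected newborns would take 323 cases at 70% sensitivity for ±5, or 217 at 90% for ±4. That conclusion needs no prevalence figure, only the judgement that an unselected birth cohort will not be 63% to 94% preterm, or 63% to 94% of low birth weight.

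The size of the shortfall does depend on prevalence. Assuming 10% to 25% affected, the half-width is about 10 to 15 points at 70% sensitivity and 6 to 10 points at 90%, or 2 to 3.2 times the width with 342. The Protocol's own exclusions of perinatal deaths and of some very sick babies would tend to lower the case count, since its Background names both conditions as main contributors to neonatal mortality.

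Because this sentence is the sole justification of size for the primary outcome, it should be corrected.

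**What to change.** **Sample size section.** Remove the statement that ±4 to 5% will be achieved. Give instead the assumed prevalence and expected number of cases for preterm birth and for low birth weight separately, with the half-width for each. Illustrative wording: *with 10–20% of newborns affected (34–68 cases), the 95% confidence interval for a sensitivity of 70–90% will be about ±7 to 15 percentage points*. The source of the prevalence should be named, since the Protocol currently has none. If precision for specificity is added, compute it on unaffected newborns: about ±3.4 to 5.4 points with 274–308 of them, for specificity of 90% down to 70%.

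**Statistical analysis section, as a clarification.** Define sensitivity as the proportion of affected newborns below the cut-off, and specificity as the proportion of unaffected newborns at or above it, for each target condition. Any cut-off reported for very low birth weight should carry its case count and an exact interval.

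**Cost.** Rewording only, and a less favourable stated precision. No extra participants are needed. Enlarging the study to keep ±5 points at 70% would take 1,291 newborns at 25% prevalence and 3,227 at 10%, which is not realistic when enrolment is limited by the parent trial's deliveries.

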## Statistical analysis

I will examine the distributions of each variable. I will describe continuous variables using histograms, mean and standard deviation, and median and interquartile range. I will describe frequencies of categorical variables as percentages. I will conduct a descriptive analysis to examine associations with preterm delivery and low birth weight, including social and demographic factors (collected during WANTAIM assessments) and achievement of developmental milestones at 6 months and between study arms and achievement of developmental milestones at 6 months. I will assess the correlation between the gestational age at birth (measured by USS) and birthweight (measured using digital scales) and anthropometric measures (foot length, head circumference, MUAC) using Spearman’s rank correlation coefficient.

I will calculate diagnostic performance of foot length as: a) sensitivity (proportion of newborns correctly identified as preterm, low birthweight or very low birth weight); and b) specificity (proportion of newborns correctly identified as not preterm or not low birth weight) for 1mm increments in foot length. I will also calculate sensitivity and specificity for head circumference (1.0cm increments) and MUAC (1mm increments).8

To assess the diagnostic performance of each anthropometric measure as a predictor of preterm birth, low birth weight and very low birth weight, I will construct receiver operating characteristic (ROC) curves.24 The ROC curve is a graphical plot of sensitivity (vertical axis) against 1 minus specificity (horizontal axis) for each increment in measurement of the anthropometric measure. The best cut-off for each measure is the value at which the sensitivity and specificity are highest. I will then calculate the area under the curve (AUC, with 95% confidence intervals) as a proportion of the total area. The closer the AUC value is to one, the better the predictive value.

I will provide the best cut-off for the prediction of preterm birth, low birth weight and very low birth weight using foot length, head circumference and MUAC. I will recommend the most appropriate and simple measure based on my findings.

I will use linear regression to examine associations between the foot length at birth and achievement of developmental milestones, with multivariable models to control for potential confounding.

For the assessment of reliability of foot length measurement, I will calculate κ based on the expected and observed frequencies for the agreement of measurements and plot the difference between the raters against the average measurement of the two raters (Bland-Altman plot).24

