The Women And Neonatal Trial of Antenatal Interventions and Management (WANTAIM) is a randomized cluster crossover trial of the effectiveness of point-of- care testing for sexually transmitted infections in pregnancy to improve birth outcomes. The prevention of adverse outcomes, such as preterm birth, low birth weight, neonatal eye infections and neonatal pneumonia should contribute to improved infant health. The trial enrols women attending antenatal clinics and includes assessment of gestational age by USS and neonatal examination within 72 hours of birth. This setting allows for assessment of both anthropometric measurements, including foot length, within 72 hours of birth and follow up of physical growth and development outcomes beyond the neonatal period in a community-enrolled sample. Such information will contribute to evidence needed to assess the burden of disease due to preterm birth and low birth weight.6

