## Study setting

The Neonatal Foot Length (Neofoot) study will be conducted as a sub-study of the Women and Newborn Trial of Antenatal Interventions and Management (WANTAIM) in three WANTAIM trial sites in Madang Province.

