## Eligibility criteria

Women enrolled in the two WANTAIM sites will be eligible if they have complete data on USS assessment of gestational age and have a post-natal visit completed within 72 hours of birth. Women whose baby died in the perinatal period, or who have very sick babies or babies with congenital abnormalities that restrict team from collecting outcomes within 72 hours of birth, or who will be moving out of the catchment area within the next 6 months, will be excluded. Locator information for eligible participants, collected at WANTAIM enrolment will be updated.

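### The protocol gives both three and two study sites, and its descriptive comparison of 6-month milestones by WANTAIM arm names no site or period although arm is allocated by cluster crossover

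*Protocol*

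**What the plan says.** On the number of sites, the protocol speaks twice:

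- Study setting: the sub-study runs in "three WANTAIM trial sites in Madang Province".
- Eligibility criteria: "Women enrolled in the two WANTAIM sites will be eligible", subject to further conditions.

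The Sample size section projects 400 invitations from expected trial enrolment at the study clinics. It gives neither the number of clinics nor a figure per site.

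On study arm:

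- Background: the parent trial, WANTAIM, "is a randomized cluster crossover trial".
- Study Objectives, secondary objective 4: associations between foot length at birth, "physical growth and development of the infant at 6 months, according to study arm".
- Statistical analysis: the sentence that opens "I will conduct a descriptive analysis to examine associations" ends by including the comparison "between study arms and achievement of developmental milestones at 6 months".

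No site, cluster or period term is named for that comparison. The only adjustment mentioned is in the multivariable models for foot length and milestones, and their covariates are not listed. The protocol does not say which arm each site is in, when sites cross over, or whether Neofoot recruitment spans a crossover.

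**The concern.** The two site counts cannot both be right, and they define different populations. A woman enrolled at the third site is inside the study by one section and outside it by the other. The 400, and the 342 and 274 derived from it, depend on which clinics were counted.

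The arm comparison raises a related difficulty. In a cluster crossover trial, arm belongs to a site in a given period, not to an infant. With only two or three sites, a difference in milestones between arms may reflect the sites or the calendar. How far it does so depends on the site count and on the timing of the crossover. The first is contradictory and the second is not given. At stake is that a site or period difference could be read as an effect of the WANTAIM intervention on infant development.

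**Working it through.** **The plan's own figures.** 400 × 0.95 × 0.90 = 342, and 342 × 0.80 = 273.6, which rounds to 274. Both stated numbers reproduce. The projection of 400 means 400/2 = 200 invitations per site with two sites, or 400/3 ≈ 133 with three. The protocol does not say which was meant.

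**Confounding by layout.** I take each site to be one cluster, which the protocol does not state, and assume equal recruitment in every site-period cell. No intracluster correlation is needed here.

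1. *No crossover within recruitment.* Each site is seen in one arm only. With two sites there is at most one site per arm; with three, at best two against one. Arm is a function of site, and no adjustment can separate them.
2. *Three sites, all crossing over.* Each site contributes equally to both arms, so site cancels. Period does not, because three sites cannot split evenly between two sequences. At best two sites start in arm A and one in arm B. Then 2/3 of arm A and 1/3 of arm B fall in period 1. A period difference d adds (2/3 − 1/3) × d = d/3 to the raw arm contrast.
3. *Two sites, crossing over in opposite sequences.* Site and period both cancel in the raw contrast.
4. *All sites crossing in the same sequence.* Arm coincides with period.

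**What adjustment leaves.** For two sites over two periods there are 4 cells and 4 parameters (intercept, site, period, arm), so 4 − 4 = 0 between-cluster degrees of freedom remain. For three sites there are 6 cells and 5 parameters (intercept, two for site, period, arm), which leaves 6 − 5 = 1. A formal test of arm would have almost nothing to rest on.

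**Size, on assumed values.** The protocol gives no intracluster correlation (ICC). I assume 0.01 to 0.05, and a between-period correlation ratio (CAC) of 0.5 to 1.0.

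- No crossover in the window: DE = 1 + (m − 1) × ICC, with m = 274/sites.
- Every site seen in both periods: DE = 1 + (m − 1) × ICC − m × ICC × CAC, with m = 274/(2 × sites).

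| Layout | m | Design effect (DE) | Effective N (274/DE) |
|---|---|---|---|
| Two sites, no crossover | 137 | 2.36 to 7.80 | 116 to 35 |
| Three sites, no crossover | 91.3 | 1.90 to 5.52 | 144 to 50 |
| Two sites, crossover | 68.5 | 0.95 to 2.66 | 288 to 103 |
| Three sites, crossover | 45.7 | 0.95 to 2.09 | 288 to 131 |

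Example for three sites crossing over, ICC 0.05 and CAC 0.5: 1 + 44.7 × 0.05 − 45.7 × 0.05 × 0.5 = 2.09. With CAC 1.0 it is 0.95; a value below 1 arises because the within-site comparison removes differences between sites. The no-crossover rows show loss of precision only. They do not mean that the arm effect could be recovered from a larger sample.

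**The case against.** The strongest reply is that no intervention test is planned. The comparison sits inside an analysis labelled descriptive, with no test, significance level, interval or power attached. The study is a diagnostic-accuracy cohort sized on the precision of sensitivity. The Sample size section's remark on power for secondary outcomes takes foot length by milestone status as its example, not arm. Secondary objective 4 can be read as stratifying by arm. The handling of clustering could properly sit in an analysis plan that is not shown, and the unlisted covariates of the foot-length models do not exclude site and period.

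Most of this stands, and it rules out three stronger readings that a reader might infer:

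- *That false-positive rates are inflated or intervals too narrow.* This presumes a test that treats the 274 infants as individually randomised. The protocol does not say that it will do this.
- *That any arm difference is mixed with site and period.* A balanced two-site crossover can cancel both, and the disagreement over site count does not itself cause confounding. Nor is the usual parallel-cluster design effect right for sites that cross over, because it ignores that each site contributes to both arms.
- *That 400 is wrong or out of reach.* The protocol does not show what site count lay behind it, so it can be confirmed but not recalculated from the text.

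Two things remain. The site contradiction concerns setting and eligibility, which belong to the protocol whatever an analysis plan contains. And a descriptive label removes the test but not the confounding: a raw contrast by arm can still be read as an intervention effect.

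**Conclusion.** The site contradiction is certain from the text and leaves the eligible population, and the basis of the 400, unclear.

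The arm comparison is a conditional problem. With two or three sites a raw contrast is wholly confounded with site if no crossover falls within recruitment. If three sites cross over, at best one third of any period difference enters it. With two sites in opposite sequences, both can cancel. Which case applies cannot be told from the protocol. These statements assume one cluster per site and equal recruitment per cell.

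The design effects (about 0.95 to 2.1 for three sites crossing over, 1.9 to 5.5 for three sites without a crossover in the window) rest on an assumed ICC and, in the crossover case, an assumed between-period correlation. They are illustrations, not corrections to a stated figure. The point touches eligibility and secondary objective 4; the primary accuracy objective does not depend on the arm comparison.

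**What to change.** 1. State the number of sites once, make Study setting and Eligibility criteria agree, and confirm in Sample size that the projection of 400 refers to those sites.
2. State which WANTAIM arm each site is in, by period, during Neofoot recruitment.
3. Show the descriptive arm results as counts by site and period, without tests.
4. Include site and period as terms in the 6-month models.
5. Where no site is observed in both arms, state that the arm comparison cannot be separated from site.

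The cost is a few sentences and two model terms. The arm results lose apparent precision.

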# Ethical considerations

There are no major study-related risks for participants involved in this study. We will be using a stiff clear plastic ruler to measure the foot length and tape measure to measure head circumference and MUAC. This is a non-invasive assessment with no associated risk. At 6 months, babies will be assessed for their physical growth using scales, measuring mat, thermometer, stethoscope, measuring tapes, which are used at health facilities every day to assess children.

Neonates born to mothers participating in the WANTAIM trial will be included into the study and followed up at 6 months. Their interest will be protected by way of taking written informed consent. Parents/caregivers will consent on behalf of the child, given the age of the participant involved in the study, at the 72-hour post-natal visit. The parent/caregiver will be informed that their child’s participation is voluntary and that he/she may withdraw the child from the study at any time. Only the researchers will have access to the information obtained from participants. The identity of participants will not be revealed. All participants will be assigned an ID code and this information will always be kept confidential.

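### Head circumference is analysed in 1.0 cm steps against 1 mm for foot length and MUAC, a small but one-directional handicap in the three-way comparison

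*Protocol*

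**What the plan says.** Secondary objective 1 (Protocol, Study Objectives) is: "Compare foot length, MUAC and head circumference as predictors of preterm birth and low birth weight".

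The Statistical analysis section fixes the steps. Sensitivity and specificity are calculated "for 1mm increments in foot length", and then: "I will also calculate sensitivity and specificity for head circumference (1.0cm increments) and MUAC (1mm increments"). The next paragraph describes the ROC curve as sensitivity plotted against 1 minus specificity "for each increment in measurement of the anthropometric measure". The cut-off rule is: "The best cut-off for each measure is the value at which the sensitivity and specificity are highest". AUCs with 95% confidence intervals follow, a value nearer one being taken as better. The section then says: "I will recommend the most appropriate and simple measure based on my findings".

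On instruments, Ethical considerations names a stiff plastic ruler for foot length and a "tape measure to measure head circumference and MUAC".

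**The concern.** The three measures are to be compared on the same babies, but one is placed on a grid ten times coarser in absolute terms. Grouping a measurement removes points from its ROC curve. Straight lines between the remaining points lie below a concave curve, so the trapezoidal AUC falls. The candidate cut-offs are also limited to whole centimetres. Both effects run against head circumference.

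Equal absolute steps are not needed in themselves, because head circumference varies more than foot length. What counts is the step relative to the spread, and that is what the working checks. At stake are secondary objective 1 and the cut-off reported for head circumference.

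**Working it through.** **The plan's own number.** From Sample size, "an estimated 400 women will be invited to participate", with 95% visited and 90% agreeing: 400 × 0.95 × 0.90 = 342, as stated. The protocol gives no figure for the effect of step size, so there is nothing further to reproduce.

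**Inputs.**
- From the protocol: steps of 1.0 cm (head circumference) and 1 mm (foot length, MUAC); n = 342.
- Assumed: within-group SD of 1.2-1.8 cm for head circumference, 0.45 cm for foot length and 0.9 cm for MUAC; true AUC 0.80 for each measure; 10-20% cases.

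**Step in SD units** (step ÷ SD).
- Head circumference: 1/1.8 = 0.56 to 1/1.2 = 0.83.
- Foot length: 0.1/0.45 = 0.22.
- MUAC: 0.1/0.9 = 0.11.

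Even after allowing for its larger spread, head circumference is on a grid about 2.5 to 3.8 times coarser than foot length (0.56/0.22 to 0.83/0.22).

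**AUC.** With normal distributions of equal variance, the separation is δ = √2 × Φ⁻¹(0.80) = 1.4142 × 0.8416 = 1.190. At grid points c spaced one step apart, the false-positive rate is Φ(c) and the sensitivity Φ(c + δ). The grouped AUC is the trapezoidal sum of these points, averaged over where the grid happens to fall.

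| Measure | Step, SD | AUC | Loss |
|---|---|---|---|
| Head circumference | 1.0 cm, 1.2 cm | 0.787 | 0.013 |
| Head circumference | 1.0 cm, 1.5 cm | 0.7915 | 0.0085 |
| Head circumference | 1.0 cm, 1.8 cm | 0.794 | 0.006 |
| Foot length | 1 mm, 0.45 cm | 0.799 | 0.001 |
| MUAC | 1 mm, 0.9 cm | 0.800 | 0.0002 |
| Head circumference, if 1 mm | 0.1 cm, 1.2-1.8 cm | 0.800 | about 0.0001 |

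Over true AUCs of 0.75-0.95 the head-circumference loss is 0.004-0.014, always in the same direction.

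**Cut-off.** The protocol's rule is read here as the maximum of Youden's J (sensitivity + specificity − 1). At the optimum both are Φ(δ/2) = Φ(0.595) = 0.724, so J = 0.448. In the worst case the nearest whole centimetre is half a step away, h = 0.5/SD, and J = Φ(0.595 − h) + Φ(0.595 + h) − 1.

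| SD | h | Lower of the two | Higher of the two | J | Loss of J |
|---|---|---|---|---|---|
| 1.2 cm | 0.417 | 0.571 | 0.844 | 0.415 | 0.033 |
| 1.5 cm | 0.333 | 0.603 | 0.823 | 0.427 | 0.022 |
| 1.8 cm | 0.278 | 0.625 | 0.809 | 0.433 | 0.015 |

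At SD 1.5 cm, sensitivity and specificity each move 10-12 points, in opposite directions (72/72 becomes 60/82 or 82/60). Over SD 1.2-1.8 cm the movement is 8 to 15 points.

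**Against sampling error.** The Hanley-McNeil standard error of a single AUC of 0.80 at n = 342 is 0.047, 0.038 and 0.034 for 10%, 15% and 20% cases. The largest loss is 0.013/0.034 = 0.39 of a standard error.

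**Effect on ranking.** I simulated 3,000 studies with n = 342, 15% cases, true AUC 0.80 for all three measures and within-group correlation 0.6, taking head-circumference SD as 1.5 cm. Head circumference had the highest AUC in 24-25% of studies with 1.0 cm steps and in 35% with 1 mm steps. A fair share is 33%.

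**The case against.** **The AUC effect depends on a reading.** The 1.0 cm step is attached to the sensitivity and specificity calculation. The phrase about each increment, one paragraph later, could be a textbook description of a ROC plot. The protocol does not say that the AUC will be computed from grouped values or by the trapezoidal rule. This stands as a caution. The carry-over is the natural reading, because the increments are the only ones the section defines, but it is not spelled out.

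**It may be a slip.** 1.0 cm could be meant as 0.1 cm or 1.0 mm. If so, the bias disappears and only the text needs correcting.

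**The size is small.** This stands too. The AUC loss is well under one standard error, and the ranking result assumes three exactly equal measures, the case in which a small bias counts most. Lost sensitivity at an off-optimum cut-off is largely repaid in specificity. A full step away from the optimum, sensitivity would go from 72% to 47% or 90% at SD 1.5 cm, but a rule that picks the best available grid point would not choose that cut-off.

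**Stronger claims a reader might infer, and why they fail.**
- That every measure is read to the millimetre, so the fix needs no new data: the text names a tape but gives no reading resolution for head circumference.
- That step size decides the recommended measure: appropriateness and simplicity count as well, and AUC is not named as the criterion.
- That the measures will be judged by whether separate confidence intervals overlap: the protocol does not say so. A paired comparison of AUCs is detail that a statistical analysis plan may hold, so its absence here is no finding.
- That the rounding favours foot length in particular: MUAC loses least.

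**Conclusion.** The point holds as a small, systematic and avoidable handicap. Tenfold different steps are fixed without a stated reason, and on the natural reading they reach the AUC and cut-off of head circumference alone. Under the assumed SDs and a true AUC of 0.80, head circumference loses about 0.006-0.013 of AUC, against about 0.001 for foot length and 0.0002 for MUAC. Its cut-off loses at most 0.015-0.033 of J.

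This could change the ranking only where the measures are close in accuracy. It touches secondary objective 1 and the head-circumference cut-off. The primary objective, the accuracy of foot length, already uses 1 mm steps and is unaffected. The direction held at every value tried; the size rests on SDs, AUC and case share that the protocol does not give.

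**What to change.** 1. Confirm whether 1.0 cm is intended. If it is a slip, correct it.
2. If it is intended, state that each ROC curve and AUC is built from the values as recorded, or use the same 1 mm step for all three measures. This brings the AUC loss for head circumference down to about 0.0001 and the largest loss of J to at most 0.0004.
3. Make sure that the case record form takes head circumference to the millimetre.
4. Round only the cut-off finally proposed for field use, and report its sensitivity and specificity after rounding.

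**Cost.** A sentence in the Statistical analysis section. If the form already records millimetres, nothing else changes. If it records whole centimetres, the form must be changed before data are collected, because the lost resolution cannot be recovered afterwards.
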